### Statistical analysis

#### Power calculation

The sample size was determined for the impact study to evaluate the effectiveness of the cash transfer program at improving the proportion of PLHIV with suppressed viral load (< 1000 copies/ml) at 12 months. We used estimates of viral suppression at 12 months and ICC = 0.05, estimated from a previous cluster randomized study of HIV treatment adherence that we conducted among HIV-infected pregnant women in Shinyanga Region, an ICC consistent with previous studies [52]. Using site-adjusted data about viral suppression at 6 months from phase I (75.2% in the control group), along with estimates of viral suppression decline between 6 and 12 months, we estimate that viral suppression among adults at 12 months in the comparison sites will (conservatively) be 70%. With an ICC of 0.05, 32 facilities, 80% power, and 56 PLHIV per clinic (*n* = 1792), the minimum detectable effect is 11 percentage points as an absolute reduction in the proportion experiencing viral suppression. In the second trial (optimization), we achieved a 12.6 percentage point difference with the 22,500 TSH cash transfer at 6 months, so we believe this effect size is achievable. In addition, if viral suppression is lower than expected in the comparison arm, and the effect of the intervention remains stable, power will increase. We will inflate the target sample size by 10% to *n* = 1984 (62 participants per clinic across 32 clinics) to account for unexpected issues or significant differences in the enrollment between clinics.

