## Methods

### Design

The study has two primary objectives:
*Impact evaluation: Evaluate the effect of the 6-month cash transfer program on viral suppression (< 1000 copies/ml) at 12 months after starting ART.*The primary objective of this study is to evaluate the effectiveness of the cash transfer program using 22,500 Tanzanian Shillings (TZS)/month (as determined by phase I) at improving the proportion of PLHIV retained on ART and with suppressed viral load at 12 months after starting ART. Using a cluster randomized control trial, with our sample size of 32 clinics and 1984 participants (62 participants per clinic), we will have 80% power to detect a risk difference (RD) of 11 percentage points in viral suppression at 12 months between the participants attending intervention and control clinics.The secondary outcomes of the impact evaluation are:
Viral suppression (< 1000 copies/ml) at 6 months;Retention on ART at 6 and 12 months;The proportion virally suppressed of those retained on ART at 6 and 12 months; andAppointment attendance, the proportion of scheduled visits that were completed during the 0–6- and 0–12-month periods.*Implementation study: Understand implementation successes and challenges through measurement of implementation outcomes, and use lessons learned to inform wider adoption of cash transfer programs for PLHIV.*Although evidence from our previous studies demonstrates the preliminary effectiveness of cash transfers on HIV-related outcomes, we do not yet know the optimal strategy for implementing this type of system at a larger scale and outside of a research setting. Thus, in anticipation of the potential adoption of the program by the Ministry of Health or others, a primary objective of this study is to gather information related to successful implementation practices and challenges needing attention before scaling.

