### Randomization and masking

Once facilities are selected for the study and have agreed to participate, we will randomize 32 facilities to either the SOC or the cash transfer intervention group at UC Berkeley using the cvcrand package (cvrall command) in R statistical software [46]. To ensure that the arms are balanced on important covariates, and to mitigate the possibility of ineffective randomization due to the small numbers of clinics in the study, we will use a constrained randomization process [47]. This process essentially pre-determines a set of acceptable allocations into intervention and control clusters based on covariates of relevance and then randomly selects an allocation from the list of acceptable allocations [47]. Specifically, based on our experience in phase 1, we will include the following covariates in the constrained randomization process: geographic region (Geita, Kagera, Mwanza, or Shinyanga), facility level (hospital, health center, or dispensary), driving distance to a major city (km), proximity to a major road (< 5 km), and average number of ART initiates per quarter. We will stratify on geographic region. The 32 sites will be randomized 100,000 times, and we will select the unique schemes as the randomization space. Those iterations with an l2 balance score less than the *q* = 0.1 cutoff will be retained. Among those remaining iterations where there was little to no imbalance detected, we will check for validity of the constrained randomization (e.g., no deterministic allocation of clusters into arms) and ensure that there are sufficient constrained randomizations from which to randomly select a single randomization scheme.

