#### Data analysis—impact study

We will conduct an intent-to-treat analysis to determine the effect of the intervention on 12-month viral suppression (the primary outcome). We will conduct a cluster-based permutation test on the individual-level outcome data, which accounts for clustering within the clinic. The effect estimate of interest is the risk difference of viral suppression among PLHIV attending intervention versus comparison facilities. We will pre-register our analysis plan at AsPredicted.

We will conduct several secondary analyses of the primary outcome, although we are not powered for these analyses. We will examine heterogeneity in the primary analysis by facility and patient characteristics. We will also conduct a treatment-on-the-treated analysis to isolate the impact of incentive delivery [53–55].

Using the same methods as for the primary analysis, we will also assess effects on the following key secondary outcomes:
Viral suppression (< 1000 copies/ml) at 6 months;Retention on ART at 6 and 12 months;The proportion virally suppressed of those retained on ART at 6 and 12 months; andAppointment attendance, the proportion of scheduled visits that were completed during the 0–6- and 0–12-month periods.

We will additionally assess effects on the following survey-based outcomes at 6 and 12 months:
Food securityMental health (anxiety, depression)HopefulnessIPVSelf-efficacyParticipation in the labor force/functional statusOther indicators of household welfare (e.g., investment in small businesses)

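### The power section says a lower control-arm suppression rate with a stable effect raises power; on the plan's own risk-difference scale power falls, from about 80% to about 72% at a 60% control rate

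*Protocol article*

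**What the plan says.** The Power calculation section plans on the assumption that "viral suppression among adults at 12 months in the comparison sites will (conservatively) be 70" per cent. It then sets the design: "With an ICC of 0.05, 32 facilities, 80% power, and 56 PLHIV per clinic" (1792 participants), for which "the minimum detectable effect is 11 percentage points as an absolute reduction in the proportion experiencing viral suppression". The target is inflated by 10% to "62 participants per clinic across 32 clinics" (1984). After noting that the optimization trial achieved a 12.6-point difference at 6 months, the paragraph adds that "if viral suppression is lower than expected in the comparison arm, and the effect of the intervention remains stable, power will increase". It does not say on which scale the effect is to remain stable.

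Two other sections fix the scale. Design states that "we will have 80% power to detect a risk difference (RD) of 11 percentage points in viral suppression at 12 months". Data analysis—impact study states that "The effect estimate of interest is the risk difference of viral suppression among PLHIV attending intervention versus comparison facilities". No odds ratio, risk ratio or relative reduction in failure is named for the primary outcome.

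**The concern.** For a binary outcome, the variance of a difference in proportions depends on where the two proportions lie. Here they are 70% and 81%, both above 50%. If the control rate drops and the risk difference stays at 11 points, both proportions move towards 50%, where p(1−p) is largest. The standard error rises, the difference to be detected does not, and power is lost. The sentence claims the opposite.

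This is the only remark in the power section on what happens if the control rate is missed on the low side. The 70% is itself a projection, taken from 75.2% at 6 months and an expected decline by 12 months. The sentence therefore presents as helpful a scenario in which the stated 80% would not be met.

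The same paragraph also describes the detectable effect as a reduction in suppression, although the trial aims to improve it.

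**Working it through.** **Inputs**
- From Power calculation: control rate 70%, effect 11 points, ICC 0.05, 32 clinics, 56 per clinic (62 after inflation).
- From Design and Data analysis—impact study: the effect is a risk difference, and the aim is improvement, so 70% vs 81%.
- Assumed: two-sided 5% (the article does not give alpha) and 16 clinics per arm (Randomization and masking says "we will randomize 32 facilities to either the SOC or the cash transfer intervention group" without a ratio). One-sided 5% would give 87.7% power and does not reproduce the stated 80%.

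**Formulas**
- Design effect DE = 1 + (m − 1) × ICC
- Effective n per arm = 16 × m / DE
- SE = √{[p₀(1 − p₀) + p₁(1 − p₁)] / n}
- Power (unpooled) = Φ(|p₁ − p₀| / SE − 1.96). The pooled version uses the pooled variance under the null hypothesis for the critical value.

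**Step 1: reproduce the plan's figure**
- DE = 1 + 55 × 0.05 = 3.75; effective n = 896 / 3.75 = 238.9 per arm.
- 70% vs 81%: SE = √[(0.2100 + 0.1539) / 238.9] = 0.0390; z = 0.11 / 0.0390 = 2.82.
- Power is 80.5% unpooled and 80.0% pooled. The minimum detectable effect at 80% power is 11.0 points (pooled).

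The plan's statement is reproduced.

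**Step 2: lower the control rate and hold the risk difference at 11 points**

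For example, 60% vs 71%: SE = √[(0.2400 + 0.2059) / 238.9] = 0.0432; z = 2.55; power 72.1% unpooled.

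| Control rate | Intervention rate | Power, 56 per clinic (pooled / unpooled) | Power, 62 per clinic (pooled / unpooled) |
|---|---|---|---|
| 70% | 81% | 80.0% / 80.5% | 81.0% / 81.4% |
| 65% | 76% | 75.2% / 75.7% | 76.3% / 76.7% |
| 60% | 71% | 71.7% / 72.1% | 72.7% / 73.2% |
| 55% | 66% | 69.2% / 69.7% | 70.3% / 70.8% |
| 50% | 61% | 67.8% / 68.2% | 68.9% / 69.3% |

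For 62 per clinic, DE = 1 + 61 × 0.05 = 4.05 and effective n = 992 / 4.05 = 244.9 per arm, so the 10% inflation adds little.

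With 56 per clinic, power keeps falling to a minimum of 67.3% (pooled) at a control rate of about 44.5%, and is still 79.0% at 20%. The minimum detectable effect rises from 11.0 points at 70% to 12.1 at 60% and 12.7 at 50% (pooled). A t reference distribution on 30 degrees of freedom lowers the level but not the direction: 77.9% at 70% and 69.3% at 60%.

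**Step 3: other meanings of a stable effect, at a 60% control rate (56 per clinic, pooled)**

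| Held constant at its 70% vs 81% value | Intervention rate | Power |
|---|---|---|
| Risk difference, 11 points | 71.0% | 71.7% |
| Odds ratio, (0.81/0.19)/(0.70/0.30) = 1.83 | 73.3% | 87.0% |
| Relative risk of non-suppression, 0.19/0.30 | 74.7% | 93.0% |
| Risk ratio of suppression, 0.81/0.70 | 69.4% | 57.8% |

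Power rises on the second and third scales because the risk difference then grows to 13.3 and 14.7 points.

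**Step 4: the word for the direction**

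Read literally, a reduction in suppression is 70% to 59%, which gives 71.1% (pooled) to 71.5% (unpooled). The stated 80% reproduces only for 70% to 81%.

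**The case against.** The strongest defence is that the meaning of stable is left open. With a constant odds ratio, or a constant relative reduction in non-suppression, the sentence is true. That stands as a limit on the point: the fault is an unnamed scale as much as wrong arithmetic. It does not rescue the sentence as written, because the plan powers and estimates the effect only as a risk difference, and the comparison immediately before the sentence is also in percentage points.

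The second defence is that little depends on it. The number of clinics, the detectable effect and the analysis do not use the sentence, and this also stands. The 60% control rate is my illustration, 10 points below the planning rate; at 65% the loss is about 5 points. If the 12.6-point difference seen at 6 months in the optimization trial held at 12 months, power at a 60% control rate would be about 83–84% with 56 per clinic.

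Some stronger readings are tempting but not supported:
- **That the paragraph contradicts itself by calling 70% conservative.** The word may only describe a cautious forecast of suppression, not caution about power.
- **That the control rate is the main planning uncertainty.** The article does not say so. By the same formula, an ICC of 0.06 instead of 0.05 takes power to about 74–75%, much the same as a 5-point drop in the control rate.
- **That a null result would be misread.** The result would be read from the estimated risk difference, which this sentence does not affect.
- **That the trial was powered for harm.** The objective is plainly improvement, and an 11-point reduction in non-suppression (30% to 19%) is the same contrast as 70% to 81%. The word is a slip.

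**Conclusion.** The point holds as an error in one stated property of the design. On the risk-difference scale that the article uses, lower control-arm suppression with an unchanged 11-point effect reduces power from about 80% to about 75–76% at a 65% control rate and about 72% at 60% (about 73% with 62 per clinic). These figures assume two-sided 5%, equal allocation, an ICC that stays at 0.05 and a normal approximation. The direction does not depend on the choice between pooled, unpooled and t-based calculation.

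A reader might infer that the trial is underpowered or its sample size wrong. That does not follow: 80% power for 11 points with 32 clinics reproduces from the plan's own inputs. Severity is minor to moderate.

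**What to change.** Delete the sentence, or replace it with wording such as: *If suppression in the comparison arm is below 70% and the risk difference remains 11 percentage points, power falls below 80% (about 75% at 65% and 72% at 60%; 56 per clinic, ICC 0.05, two-sided 5%, equal allocation, normal approximation with design effect).* The team should confirm alpha and the method before printing the figures. If a constant odds ratio or a constant relative reduction in non-suppression was meant, name that scale and give the implied risk difference.

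As a minor wording correction in the same paragraph, describe the detectable effect as an absolute increase in suppression, from 70% to 81%.

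The cost is two sentences and a slightly less favourable account of power. Sample size, outcome, randomization and analysis stay as they are.

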#### Data analysis—impact study

We will conduct an intent-to-treat analysis to determine the effect of the intervention on 12-month viral suppression (the primary outcome). We will conduct a cluster-based permutation test on the individual-level outcome data, which accounts for clustering within the clinic. The effect estimate of interest is the risk difference of viral suppression among PLHIV attending intervention versus comparison facilities. We will pre-register our analysis plan at AsPredicted.

We will conduct several secondary analyses of the primary outcome, although we are not powered for these analyses. We will examine heterogeneity in the primary analysis by facility and patient characteristics. We will also conduct a treatment-on-the-treated analysis to isolate the impact of incentive delivery [53–55].

Using the same methods as for the primary analysis, we will also assess effects on the following key secondary outcomes:
Viral suppression (< 1000 copies/ml) at 6 months;Retention on ART at 6 and 12 months;The proportion virally suppressed of those retained on ART at 6 and 12 months; andAppointment attendance, the proportion of scheduled visits that were completed during the 0–6- and 0–12-month periods.

We will additionally assess effects on the following survey-based outcomes at 6 and 12 months:
Food securityMental health (anxiety, depression)HopefulnessIPVSelf-efficacyParticipation in the labor force/functional statusOther indicators of household welfare (e.g., investment in small businesses)

#### Data analysis—implementation study

Following each in-depth interview, the interviewer will memo then debrief with the study team to discuss emergent themes. Debriefings will be held weekly with interviewers and the PI to ensure consistency and quality of data collection. Audio-recordings from IDIs will be verbatim transcribed and translated into English. Data analysis will follow an open-coding approach [56, 57] and will be based on research questions, study aims, and Proctor’s implementation constructs. An initial coding framework will include a list of predefined analytical terms relating to Proctor’s constructs; however, data analysis will be iterative, allowing new themes to emerge throughout the analysis process [58]. Data will be coded independently by two members of the research team using Dedoose qualitative coding software. Concepts will be grouped into categories, and main themes will be extracted and summarized in an analytic theme matrix.

Implementation outcome data from structured surveys with clinical staff will be analyzed descriptively using both STATA and Dedoose. We will synthesize quantitative and qualitative data to produce a comprehensive set of implementation outcome indicators. We will then use the implementation indicators to assess variation in how the program was implemented across the intervention clinics, for example, exploring levels of penetration and fidelity of the mHealth system, and explore variation in effectiveness using a sensitivity analysis. Note that we are not powered to show statistical differences in viral suppression by variation in implementation outcomes.

## Discussion

Achieving global goals for HIV epidemic control will necessitate new implementation strategies to identify PLHIV, link them to high-quality HIV care and treatment, and retain them on lifelong ART. Cash transfers have emerged as a promising strategy worthy of consideration as part of a comprehensive approach to HIV prevention and care. We have used an iterative process grounded in implementation science approaches to demonstrate the efficacy of cash transfers for ART adherence (trial 1) [20] and optimize the cash intervention with respect to cash amount (trial 2) [19]. Now, in our third trial, we will evaluate the effectiveness of cash transfers on viral suppression with a contemporaneous assessment of implementation outcomes with the goal of preparing the intervention for scale in the complex context of low- and middle-income country health systems. The results from this type I hybrid implementation–effectiveness trial will provide much-needed data on not only the real-world effectiveness of cash transfers for ART adherence and viral suppression, but also the implementation challenges and successes that will facilitate or hinder wider scale-up within Tanzania and beyond.

The hybrid implementation science/effectiveness approach will permit (a) a contribution to what is known about the use of short-term cash transfers for PLHIV in a real-world setting in sub-Saharan Africa, including their *long-term effects on viral suppression*, and (b) an understanding of how to optimize implementation approaches, and thus, provide guidance for policymakers in facilitating successful scale-up. These results have the potential to provide the evidence needed to show that short-term assistance confers lasting benefits for those starting treatment, providing needed support as they begin to feel the beneficial effects of ART. Furthermore, the study is based in the Lake Zone region of Tanzania, a region that faces challenges common throughout sub-Saharan Africa: a shortage of skilled personnel, poverty and food insecurity, and pervasive challenges with retention in care. For these reasons, our results are likely to have a high level of external validity and policy relevance in sub-Saharan Africa.

We have intentionally designed the hybrid trial to be largely self-sufficient—that is, clinical staff have the majority of interaction with the research participants, with support from research staff initially, and then only as needed. This approach comes with some trade-offs and limitations. First, there is the strong possibility that implementation of the intervention may differ by site. While implementation differences have the potential to dilute the effect of the cash program, for an effectiveness trial in a real-world setting, such variation will provide essential knowledge that will allow best practices and lessons learned to emerge and guide policymakers in bringing the program to scale. Second, patients attending control clinics may hear about the intervention and transfer out of control clinics and into intervention clinics. To mitigate this possibility (though this was not an issue in the first two trials), we have included a minimum geographic distance between clinics to minimize spillover effects and prevent contamination of comparison communities. In addition, as large numbers of transferring patients would compromise the integrity of the study and will create an undue burden for facility staff at intervention clinics, we will not reveal that there are intervention clinics where patients will receive cash transfers as part of the study to patients enrolling in the study at control clinics. Third, there is substantial variability over time and across clinics in the number of new ART initiates, and this variability may potentially impact the rate at which we are able to enroll patients into the study.

The results of this hybrid implementation–effectiveness trial will guide policymakers in Tanzania and elsewhere in the Region about whether this intervention should (or should not) be considered in national HIV/AIDS programs, and if it should, how implementation should proceed to optimize the effectiveness of the intervention in clinics across the country. Consequently, this effectiveness trial has been designed with an eye towards *real-world*, *future scale-up*, such that the procedures we propose to follow align as closely as possible with the National policy and consistent with what clinics would and could do outside of a research study setting.

## Trial status

Protocol version: 1.2

Recruitment start date: pending, recruitment scheduled to begin in November 2020

Anticipated recruitment completion date: May 2021

## Data Availability

Not applicable

## Abbreviations

ART: Antiretroviral therapy
PLHIV: People living with HIV/AIDS
TSH: Tanzanian Shillings
LTFU: Loss to follow-up
RA: Research assistant
CTC: Care and treatment clinic (HIV)
IS: Implementation science
TASAF: Tanzania Social Action Fund
RMO: Regional Medical Officer
HBCs: Home-based care providers
